**Study Procedures:**

Screening:

Potentially eligible participants at the recruiting clinics will be identified at their first appointment. They will already have had a semen analysis and female hormone profile. They may not have had tubal patency testing. In the absence of any risk factors for tubal blockage (known endometriosis, previous pelvic surgery or pelvic infection) they will be given an information leaflet regarding the trial. Prior to tubal patency testing, all hormone results and semen analysis will be checked and eligibility confirmed. If tubal patency has been confirmed prior to this appointment, consent can be taken once the patients have had 24hrs to read the patient information sheet and consider participation.

At the appointment for HSG, HyCoSy or laparoscopy, if tubal patency has been confirmed, patients will be invited to sign a consent form. (HSG results will be formally confirmed with the consultant radiologist after the appointment).

Informed consent:

Written informed consent of both partners will be taken by a trained and delegated member of the study team. This will be done at the time of their tubal patency test or at a follow up appointment.

A copy of the consent form will be given to the participants; one copy will be kept in the woman’s hospital notes and one will be placed in the Investigator Site File. Only members of the research team documented on the delegation log will be able to consent eligible couples for participation in the study. The consenting staff will have thorough knowledge and documented training of research governance issues surrounding consent and will be fully conversant with the study protocol.

The qualified person taking consent must explain to the potential participants that they are free to refuse any involvement within the study or alternatively withdraw their consent at any point during the study and for any reason. If there is any further safety information that may result in significant changes in the risk/benefit analysis, the patient information sheet (PIS) and Informed Consent Form (ICF) will be reviewed and updated accordingly. All participants that are actively enrolled in the study will be informed of the updated information and given a revised copy of the PIS and ICF in order to confirm their wish to continue in the study (if feasible), if it may change their willingness to participate. Participants who speak limited English can only be consented and included in the trial if translation has been provided by an independent translator (i.e. not a family member) or through the Language Line translation service for UK sites. International sites have the option to translate patient-facing documentation into the required language.

Care Pathway:

Couples with unexplained infertility seen at our unit will be offered the option of self-funded IUI treatment or IVF treatment (NHS or self-funded depending on meeting eligibility criteria). Involvement in this trial will be offered to them as an option prior to self-funded treatment or whilst awaiting NHS-funded IVF treatment for which the waiting time is longer than 3 months.

Randomisation:

A computer programme will be used to randomly allocate each trial ID number to a group and patients will be randomly allocated a trial ID number using choice of a paper ticket.

Blinding: It will not be possible to blind the doctors to whether the patients have received treatment or not. The chief investigator will be responsible for organising prescriptions and given the lack of placebo, will know whether the patient has been allocated to the treatment or control group.

Trial Intervention/allocation:

Participants in the treatment arm will receive 400mg Cyclogest pessaries and will be asked to take these twice a day from 24hrs after their LH surge is detected with ovulation kits. 14 days after starting the Cyclogest they will perform a home pregnancy test and inform us of the results. If they are pregnant they will continue Cyclogest for a further 38 days as pregnancy support.

Participants in the control arm will record the time of their LH surge and perform a home pregnancy test 14 days later if their next menstrual period has not started.

All participants will be asked to attend the hospital for a mid-luteal serum progesterone test 7 days after the LH surge is detected in the first cycle only.

Monitoring Adherence

Follow-up:

Participants will be asked to email a trial-specific, secure NHS.net email address with details of their cycles – dates for LH positive results and menstrual period start dates. They will use their trial number rather than identifiable personal data. They will have consented to being contacted by either telephone or email to remind them and ask for their data. They will be reminded a maximum of twice per cycle and if they do not respond it will be assumed that they have withdrawn from the trial.

Start dates of each cycle and each LH surge will be recorded. Participants will attend the phlebotomy department at the Homerton for their mid-luteal progesterone and will have consented to the trial team accessing their records to obtain the result.

Data Collection:

The following data will be collected:

Results from hormone profile and tubal patency tests and semen analysis will have been checked prior to consent – this information would be accessed by the clinical team regardless as part of their clinical care.

Basic demographic data, fertility/ menstrual/gynaecological history, relevant medical history, allergies and medication history, dates of menstrual cycles and LH surges and clinical outcomes.

This data is routinely recorded in a patient’s notes and consent will be obtained to access this. Dates of menstrual cycle and LH surges will be requested from patients during the trial.

Identifiable data will be stored in a password protected recruitment log at site but data entered into the database will be pseudo-anonymised (identified only by a participant’s trial ID).

Participant withdrawal:

Participants will have the option to withdraw at any point during the trial and can do so by contacting the team either by email or telephone.

If at any point during the trial, a participant does not reply to two consecutive requests for results it will be assumed that they have withdrawn and no further attempts at contact will be made.

End of Study Definition:

This will be the date six weeks after the expected date of delivery of the last patient randomised who has an ongoing pregnancy.

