| Methodology | Single centre, parallel arm randomised controlled trial. Following informed consent, participants will be randomised to 3 cycles of treatment or no treatment. Primary outcome is live birth rate.  Each month participants will be asked to record the first day of their menstrual period. On the relevant cycle day according to the test instructions they will start doing daily LH monitoring using a quantified validated test (same brand) until a positive result is seen. 24hrs later they will start 400mg bd progesterone (Cyclogest) pessaries (vaginal or rectal) and continue these for 14 days. After 7 days they will attend for a serum progesterone level blood test. They will then check a urine pregnancy test (validated, same brand) on the 14^th^ day after starting cyclogest (15^th^ day after LH surge). They will discontinue the progesterone if hcg is negative and those who are pregnant will continue progesterone for 38 days. 2 weeks later they will be offered an early pregnancy ultrasound.  We will gain consent to check NHS records to record live births 42 weeks after the positive pregnancy test. We will ask patients to contact us if they have a miscarriage or late pregnancy loss but will not contact them to chase for information as this does not directly impact on our measurable outcomes (clinical pregnancy rates and live birth rates). |
| Research Sites | Homerton University Hospital |
| Objectives/Aims | To assess whether luteal support with progesterone pessaries affects the likelihood of clinical pregnancy and/or live birth in natural cycles for couples with unexplained infertility |
| Number of participants/patients | 200 in total – 100 in the test group and 100 in the control group |
| Main Inclusion Criteria | Female:   - bilateral patent tubes within last 12 months (HSG/HyCoSy/Laparoscopy) - Ovulation as defined by regular cycles or ultrasound appearance of either a corpus luteum or dominant follicle or midluteal progesterone over 30nmol/ml - Regular intercourse and failure to conceive for at least 12 months   Male:   - Semen analysis with: - >15 mil/ml concentration - Motility over 40% - Progressive motility over 32% - ≥ 4% normal forms - No erectile dysfunction or other problem preventing penetrative intercourse |

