**Results Analysis**

Sample size

According to a randomised controlled trial comparing expectant management with stimulated cycle IUI treatment over 3 cycles, 7% of the expectant management group reported live births compared to 24% of the treatment group^7^. The study identified that gave progesterone supplementation in natural cycles also showed a 24% clinical pregnancy rate (live birth rate was not reported).

Using a baseline expected live birth rate of 7% and an expected live birth rate of 24% in the treatment group, with an α0.05 and 80% power, we need to recruit 70 participants to each group. Assuming a drop out rate, we will aim to recruit 100 per group, as was recruited in the Farquhar trial.

Method of Analysis

We have adequate statistical analysis experience within the research team to analyse the data.

Analyses will be intention-to-treat, will include all randomised participants and will analyse according to the treatment group to which they were randomised. For each analysis we will present treatment effect (risk ratio)) along with a 95% confidence interval and a two-side p-value. A P value of <0.5 will be considered statistically significant.

Baseline demographic data will be assumed to be equivalent between the two groups due to the randomisation process.

For each of the outcomes measured (livebirth rate, biochemical pregnancy rates, clinical pregnancy rate, mid-luteal serum progesterone levels and pregnancy loss rates) we will perform a logistic regression, initially doing a univariable regression for each of the potential confounders AMH level, 3 vs no ovulatory cycles according to LH kits, antral follicle count, parity) and combining these together with a variable representing group using lasso or stepwise regression we will perform a multivariable logistic regression analysis.

We will validate the model, looking at calibration and discrimination by providing the c-statistic equivalent to the area under the ROC curve.

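### Silence is treated as withdrawal and no live-birth record check is provided for women who go silent before reporting a positive test, so the primary outcome can be lost despite the planned record consent

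*Protocol*

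**What the plan says.** **When a woman is presumed withdrawn.** Protocol, Study Procedures, states the rule twice. Under Follow-up: "They will be reminded a maximum of twice per cycle and if they do not respond it will be assumed that they have withdrawn". Under Participant withdrawal, once two requests in a row have gone unanswered, "it will be assumed that they have withdrawn and no further attempts at contact will be made". Requests may go by either channel: "They will have consented to being contacted by either telephone or email to remind them and ask for their data".

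**How live birth is found.** The synopsis (Methodology row) says: "We will gain consent to check NHS records to record live births 42 weeks after the positive pregnancy test". Methodology, Study design, follows women to the end of the third cycle and makes later follow-up conditional on pregnancy. The end-of-study definition also depends on the last randomised patient with an ongoing pregnancy.

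**How pregnancy becomes known.** Under Trial Intervention/allocation, treated women are told that "they will perform a home pregnancy test and inform us of the results". Control women are to "perform a home pregnancy test 14 days later if their next menstrual period has not started"; that text does not explicitly ask them to report the result.

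**Who is analysed.** Results Analysis, Method of Analysis: "Analyses will be intention-to-treat, will include all randomised participants", in the group to which they were randomised.

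**The concern.** The requests that a silent woman leaves unanswered are largely for cycle and LH-surge dates. The consequence is presumed withdrawal from the whole trial, primary outcome included. If she conceives without having reported a positive test, there is no test date from which to count 42 weeks, and the protocol provides no other look-up.

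The analysis needs a live-birth status for every randomised woman, and the collection rule does not supply one. A statistical analysis plan can choose how to handle missing outcomes, but it cannot recover births that were never sought. Much of this loss is avoidable, because a record search does not need the woman to reply.

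The trial has no placebo, and reporting differs between arms. A treated woman has an explicit instruction to report her test. If pregnant, she also continues trial drug, which gives her a practical reason to stay in touch. A control woman has neither. On the other side, treated women carry the heavier daily burden and may drop out of contact more. Ascertainment of the primary outcome could therefore differ by arm, and the direction cannot be known in advance.

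**Working it through.** **Inputs from the protocol (Results Analysis, Sample size).** Live birth 7% versus 24%, alpha 0.05, 80% power, 70 per arm, raised to 100 per arm for an unstated drop-out rate. The two-sided test is from Method of Analysis. All loss rates below are assumptions.

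**1. The plan's own figure.** Pooled two-proportion formula, two-sided, no continuity correction:

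n = [1.960·√(2·p̄·(1−p̄)) + 0.842·√(p₁(1−p₁) + p₂(1−p₂))]² / (p₂ − p₁)²

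With p̄ = 0.155: √0.26195 = 0.5118 and √(0.0651 + 0.1824) = 0.4975, so n = (1.0031 + 0.4187)² / 0.0289 = 69.95, that is 70 per arm. This reproduces the stated figure. Since 70/(1 − 0.30) = 100, the plan leaves room for 30% loss.

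**2. Power at 7% versus 24%, 100 randomised per arm, equal loss in both arms.**

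| Loss per arm | Non-responders excluded | Counted as no birth |
|---|---|---|
| 0% (all traced) | 91.9% | 91.9% |
| 10% | 89.0% | 88.3% |
| 20% | 85.1% | 83.6% |
| 30% | 80.0% | 77.6% |

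Exclusion uses n = 100(1 − loss). Counting as no birth keeps n = 100 and multiplies both rates by (1 − loss); at 30% this is 4.9% versus 16.8%.

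**3. Spurious effect when there is none.** If missing counts as no birth and all loss precedes any report, the apparent risk ratio is (1 − loss in treated)/(1 − loss in control), whatever the true common rate:

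- 10% treated, 30% control: 0.90/0.70 = 1.29
- 30% treated, 10% control: 0.70/0.90 = 0.78
- 10% treated, 20% control: 0.90/0.80 = 1.125

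**4. Loss spread over the cycles.** Suppose loss and conceptions fall evenly over three cycles. A woman lost in cycle 1, 2 or 3 then has 3/3, 2/3 or 1/3 of her possible conceptions unreported, on average 2/3. For 10% versus 30% loss: (1 − 0.0667)/(1 − 0.20) = 0.933/0.80 = 1.17.

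**5. How much the missing women could matter.** Take 7% versus 24% among responders and 100 randomised per arm. The extreme-case range of the risk difference assigns all missing women a birth in one arm and none in the other:

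- 10 missing per arm: 21.6 − 16.3 = +5.3 to 31.6 − 6.3 = +25.3 points
- 20 missing per arm: 19.2 − 25.6 = −6.4 to 39.2 − 5.6 = +33.6 points
- 30 missing per arm: 16.8 − 34.9 = −18.1 to 46.8 − 4.9 = +41.9 points

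At the loss the plan allows for, the primary comparison is no longer bounded away from zero without assumptions about the missing women.

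**The case against.** The best case for the plan is that it does not bar the look-up. The synopsis says when records are checked, not who is excluded. Clinical outcomes are among the listed data, consent to access the notes is planned, and the case report forms are completed from clinical records. The withdrawal rule ends contact and does not say that record access ends. The consent form is not available here and may separate the two. All of this stands as far as it goes: the check is unprovided rather than forbidden. The protocol still labels these women withdrawn and gives no time point for searching their records.

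Five stronger readings are tempting and should not be made:

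- *Two missed emails end participation.* The trigger is two unanswered requests, by telephone or email.
- *Every silent woman is lost.* One who reports a positive test and then stops replying may still be traced under the synopsis wording.
- *Non-responders must be excluded or counted as having no birth.* Imputation and sensitivity bounds exist and may be set out in the analysis plan.
- *The bias favours progesterone.* The documents give no loss rates. Follow-up requests go to both arms, and the withdrawal text refers to requests for results generally, so control women may in practice be asked.
- *The trial is underpowered.* At 30% loss with exclusion, power is exactly what was planned.

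It is also fair that records may be incomplete. The protocol does not say which NHS records are searched, and births elsewhere could be missed.

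**Conclusion.** The point holds as a gap in outcome collection. No live-birth check is provided for a randomised woman who goes silent before reporting a positive test, and this conflicts with the promise to analyse everyone randomised. It belongs in the protocol because later analysis cannot repair it.

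The main harm is possible bias, of unknown direction. The risk ratios of 1.29, 0.78 and about 1.17 are illustrations. They rest on assumed loss rates, no true effect, and missing counted as no birth; the first two also assume that all loss precedes any report. Excluding non-responders instead avoids bias only if silence is unrelated to live birth within each arm, which the plan gives no means of checking.

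The effect on power is secondary. Full tracing would give 91.9%, against 80.0% (excluded) or 77.6% (counted as no birth) at 30% equal loss. The 91.9% was never promised; it is what full tracing would add.

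**What to change.** 1. State under Follow-up and Participant withdrawal that non-response ends contact only, and is not withdrawal of consent for outcome data. Align the consent wording if it does not already say this.
2. For every randomised woman who has not expressly withdrawn record access, check NHS records for live birth at one fixed time from randomisation. Use the same time in both arms, long enough to cover three cycles plus pregnancy. Name the records to be searched and align the end-of-study definition.
3. Count births whose conception, dated from gestational age, falls in a pre-set calendar window from randomisation. Reported cycles cannot define the window, because non-responders have no reported cycle dates. The window also gives one rule for births from later IUI or IVF, which the care pathway makes likely for some women.
4. Report express withdrawals and untraceable women by arm.

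**Cost.** Protocol and consent wording, plus extra look-ups for at most 200 women. Births outside the records searched may still be missed, and a calendar window will misplace some conceptions near its edge, but by the same rule in both arms.

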**Results Analysis**

Sample size

According to a randomised controlled trial comparing expectant management with stimulated cycle IUI treatment over 3 cycles, 7% of the expectant management group reported live births compared to 24% of the treatment group^7^. The study identified that gave progesterone supplementation in natural cycles also showed a 24% clinical pregnancy rate (live birth rate was not reported).

Using a baseline expected live birth rate of 7% and an expected live birth rate of 24% in the treatment group, with an α0.05 and 80% power, we need to recruit 70 participants to each group. Assuming a drop out rate, we will aim to recruit 100 per group, as was recruited in the Farquhar trial.

Method of Analysis

We have adequate statistical analysis experience within the research team to analyse the data.

Analyses will be intention-to-treat, will include all randomised participants and will analyse according to the treatment group to which they were randomised. For each analysis we will present treatment effect (risk ratio)) along with a 95% confidence interval and a two-side p-value. A P value of <0.5 will be considered statistically significant.

Baseline demographic data will be assumed to be equivalent between the two groups due to the randomisation process.

For each of the outcomes measured (livebirth rate, biochemical pregnancy rates, clinical pregnancy rate, mid-luteal serum progesterone levels and pregnancy loss rates) we will perform a logistic regression, initially doing a univariable regression for each of the potential confounders AMH level, 3 vs no ovulatory cycles according to LH kits, antral follicle count, parity) and combining these together with a variable representing group using lasso or stepwise regression we will perform a multivariable logistic regression analysis.

We will validate the model, looking at calibration and discrimination by providing the c-statistic equivalent to the area under the ROC curve.

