**Methodology:**

Study design:

This study is a prospective, pragmatic, two-armed, randomised controlled trial. The hypothesised benefit of the luteal phase progesterone support is to enhance endometrial receptivity and improve conception rates measured as clinical pregnancies and eventually live births.

The study does not aim to validate different formulations of progesterone or different dosing regimens. The design of the trial supports the use of progesterone as it is licensed to be used in ART cycles, at a dose of 400mg twice per day either vaginal or rectal application.

This trial will recruit eligible participants meeting the criteria for a diagnosis of unexplained infertility. All new patients seen in the fertility units will be screened for eligibility and if eligible, will be invited to participate. Following informed consent from both partners, participants will be randomised in a 1:1 ratio to either the treatment or control groups. Women will remain in the trial for three menstrual cycles and will be followed up to the end of the third cycle. If pregnant, the outcome of the pregnancy will be recorded at 6-7 weeks of pregnancy when a scan will be performed to determine clinical pregnancy and subsequently by following up live births within 6 weeks postpartum.

Study Population:

The trial will recruit and randomise 200 participants.

Study setting:

Single centre trial at the Homerton Hospital NHS trust Fertility Unit

Inclusion Criteria:

Female:

- Bilateral patent tubes within last 12 months (HSG/HyCoSy/Laparoscopy)
- Ovulation as defined by regular cycles or ultrasound appearance of either a corpus luteum or dominant follicle or midluteal progesterone over 30nmol/ml
- Regular intercourse and failure to conceive for at least 12 months

Male:

- Semen analysis with:
- >15 mil/ml concentration
- Motility over 40%
- Progressive motility over 32%
- ≥ 4% normal forms
- No erectile dysfunction or other problem preventing penetrative intercourse

Exclusion criteria:

- Age ≥42 (as likely component in infertility),
- Unilateral tubal patency
- BMI ≥30
- Abnormal uterine cavity as seen on 3D ultrasound

Primary outcome:

Live birth rates

Secondary Outcome:

Biochemical pregnancy rates (positive urine HCG test at least 14 days after starting progesterone)

Clinical pregnancy (intrauterine gestational sac confirmed on ultrasound at 6-8 weeks gestation)

Mid-luteal serum progesterone levels

Clinical efficacy outcomes/clinical safety outcomes:

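### The protocol sets its significance threshold at P<0.5, not 0.05, so the rule as written gives about a 50% two-sided false-positive rate

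*Protocol*

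**What the plan says.** The Method of Analysis paragraph in the protocol's Results Analysis section sets out what each comparison will report: "For each analysis we will present treatment effect (risk ratio"), "along with a 95% confidence interval and a two-side p-value". The next sentence gives the decision rule: "A P value of <0.5 will be considered statistically significant".

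The Sample size paragraph of the same section uses a different error rate. It takes live birth rates of 7% and 24% and concludes "with an α0.05 and 80% power, we need to recruit 70 participants to each group". The statistical row of the synopsis repeats that alpha. No other part of the protocol states or corrects the threshold.

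**The concern.** The p-value threshold is ten times the alpha for which the trial was sized (0.5 / 0.05 = 10). It also disagrees with the interval reported beside it, because a 95% interval pairs with a two-sided test at 0.05.

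This is the rule by which the trial will say whether progesterone raises the live birth rate. Applied as written, it gives no useful protection against a chance finding, and a result could be called significant while its confidence interval lies well on both sides of a risk ratio of 1. If the threshold were instead corrected quietly once the data were in, the criterion used would not be the one in the approved protocol.

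**Working it through.** **Inputs.** From the protocol: live birth 7% (control) and 24% (treatment), alpha 0.05, power 80%, 70 per group needed, 100 per group to be recruited (Results Analysis, Sample size); 1:1 allocation (Methodology, Study design); two-sided p-value, 95% confidence interval and the 0.5 threshold (Results Analysis, Method of Analysis). Assumed, because the protocol names no test for the risk ratio: an uncorrected chi-square (pooled z) test.

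**1. Which alpha produces the stated sample size?** The usual two-proportion formula, without continuity correction, is

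n = [z(1−α/2)·√(2p̄(1−p̄)) + z(power)·√(p1(1−p1) + p2(1−p2))]² / (p2−p1)²

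with p̄ = (0.07 + 0.24)/2 = 0.155, so that √(2p̄(1−p̄)) = 0.5118 and √(0.0651 + 0.1824) = 0.4975.

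- α = 0.05: (1.960 × 0.5118 + 0.8416 × 0.4975)² / 0.17² = 2.0216 / 0.0289 = 69.95, which rounds up to **70**, the stated figure.
- α = 0.5: (0.6745 × 0.5118 + 0.8416 × 0.4975)² / 0.17² = 0.5836 / 0.0289 = 20.19, which rounds up to **21**.

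The trial was sized for two-sided 0.05, not 0.5.

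**2. False-positive rate under each threshold.** With X and Y independent binomials with the same true rate of 7%, sum the probability of every pair (X, Y) for which the test gives p below the threshold.

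| Per arm | Threshold | Any false positive | Falsely favours progesterone |
|---|---|---|---|
| 100 | 0.5 | 49.9% | 24.9% |
| 100 | 0.05 | 4.9% | 2.5% |
| 70 | 0.5 | 49.7% | 24.9% |
| 70 | 0.05 | 5.1% | 2.6% |

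With common true rates of 7%, 15.5% and 24%, the two-sided rate at 0.5 lies between 49% and 52%.

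**3. Dependence on the test.** With Fisher's exact test and a 7% rate, the 0.5 threshold gives 33% at 70 per arm and 35% at 100 per arm. A continuity-corrected chi-square gives about the same.

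**4. What would count as a positive trial?** With 100 per arm and 7 control births, z = (difference in proportions) / √(2p̄(1−p̄)/100).

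- 10 treatment births: p̄ = 0.085, z = 0.03/0.0394 = 0.76, p = 0.447. Significant under the written rule. Risk ratio 10/7 = 1.43; the log-scale standard error is √(1/10 − 1/100 + 1/7 − 1/100) = 0.472, so the 95% interval is 1.43 × exp(±1.96 × 0.472), or about 0.57 to 3.60.
- 15 treatment births: p̄ = 0.11, z = 1.81, p = 0.071. Not significant at 0.05.
- 16 treatment births: p̄ = 0.115, z = 0.09/0.0451 = 1.99, p = 0.046. The smallest count significant at 0.05.

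The excess of births needed for a positive claim falls from 9 to 3.

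**5. Several outcomes.** The Method of Analysis paragraph lists five outcomes. If they were independent (an assumption; they are in fact related), the chance of at least one false positive would be 1 − 0.5⁵ = 97% at 0.5, against 1 − 0.95⁵ = 23% at 0.05.

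**The case against.** The strongest reply is that nobody chose 0.5. Alpha is 0.05 in both sample size statements, every analysis carries a 95% interval, and the sample size fits only 0.05, so this is a dropped zero and the intent is clear. Readers would see an interval that includes 1, and the Trial Steering Committee approves the statistical analysis plan and the main paper, so the slip would probably be noticed. I accept that it is very probably a typing error and that these safeguards lower the practical risk. They do not correct the text. The error sits in the operative decision rule, and an analysis plan that used 0.05 would then contradict the protocol.

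The second reply is that the 50% depends on the test. This stands as a qualification. By Fisher's exact test, 7 against 10 births gives p = 0.61, which is not significant even at 0.5, and 7 against 16 gives p = 0.074. Even so, the false-positive rate of about 35% at 100 per arm is seven times the design alpha.

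Third, the enumeration covers one binary outcome. For the continuous mid-luteal progesterone level, a well-calibrated test would also reject about half the time under no effect; for rare outcomes such as stillbirth the rate would be lower. The 50% should therefore be read as approximate for the outcomes other than live birth.

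**Conclusion.** The concern holds. The only decision threshold in the protocol is wrong as written and conflicts with its own alpha and confidence level. Under the assumptions of 100 per arm, a 7% live birth rate in both arms and an uncorrected chi-square test, the literal rule gives a false-positive rate of 49.9%, half of it in favour of progesterone, where 0.05 gives 4.9%. A conservative exact test lowers the first figure to about 35%, which does not change the conclusion. Because this sentence governs the primary claim, it must be corrected before the analysis, however obvious the intended value.

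**What to change.** In Results Analysis, Method of Analysis, replace the threshold of 0.5 by 0.05 and say that it refers to the two-sided p-value. Keep the rule applicable to each analysis, as it is now, so that the secondary and pregnancy-loss outcomes are not left without a threshold. Make the change by a dated protocol amendment before outcome data are analysed, and use the same value in the statistical analysis plan.

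The cost is one corrected number. The sample size stands: by the same normal approximation, two-sided 0.05 gives 80.0% power at 70 per arm and 91.9% at 100 per arm for 7% against 24%. Recruitment, procedures and data collection are unaffected.

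### Female age is left off the stated adjustment list, which is itself open to data-driven selection, while baseline balance is taken for granted

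*Protocol*

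**What the plan says.** Three statements in the protocol's Results Analysis (Method of Analysis) matter here.

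- On baseline: "Baseline demographic data will be assumed to be equivalent between the two groups due to the randomisation process".
- On covariates, the candidates are listed as "potential confounders AMH level, 3 vs no ovulatory cycles according to LH kits, antral follicle count, parity".
- On model building, the plan describes "combining these together with a variable representing group using lasso or stepwise regression".

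Elsewhere in the protocol:

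- Methodology, Exclusion criteria: "Age ≥42 (as likely component in infertility". Women of any age below that limit may enter if otherwise eligible.
- Methodology, Study design: "participants will be randomised in a 1:1 ratio to either the treatment or control groups".
- Study Procedures, Randomisation: "A computer programme will be used to randomly allocate each trial ID number to a group", with ID numbers drawn as paper tickets. No stratification or minimisation by age is stated.
- Study Procedures, Data Collection: "Basic demographic data, fertility/ menstrual/gynaecological history, relevant medical history" are to be recorded.

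**The concern.** Randomisation makes the arms comparable on average over all possible allocations. It does not make the two groups actually drawn equal, so the baseline sentence asserts something that has yet to be observed.

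The wording matters because no other stated step deals with age. The design does not stratify by it, and the analysis names its covariates without it. The covariates that are named can be dropped by lasso or stepwise selection, so none that might stand in for age is sure to stay in the model.

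At stake is the live-birth risk ratio from this one trial. If one arm happens to be younger, the estimate moves and the stated model does not reliably take that out. Setting the role of age in advance also avoids a dispute, once results are known, over whether to adjust. That matters more in a trial without placebo, where about 7 live births are expected among 100 controls.

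**Working it through.** **The plan's own figure.** For 7% against 24%, two-sided alpha 0.05 and 80% power, with pooled variance under the null:

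n = [1.960 × √(2 × 0.155 × 0.845) + 0.842 × √(0.07 × 0.93 + 0.24 × 0.76)]² / 0.17² = (1.003 + 0.419)² / 0.0289 ≈ 70 per group.

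This reproduces the stated 70. Power is 80.0% at 70 per group and 91.9% at 100 per group. Nothing below changes the sample size.

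**Chance imbalance in age.** With n per arm and no stratification, the standardised difference in mean age has standard error √(2/n), and P(|difference| ≥ d) = 2 × [1 − Φ(d / √(2/n))].

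| n per arm | SE | d = 0.2 SD | d = 0.3 SD |
|---|---|---|---|
| 100 (recruitment target) | 0.141 | 15.7% | 3.4% |
| 70 (power calculation) | 0.169 | 23.7% | 7.6% |

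These cover both directions. At 100 per arm, half of 15.7%, about 7.9%, favours treatment at 0.2 SD. The 95% range at 100 per arm is ±1.96 × 0.141 = ±0.28 SD. If the SD of age is 4 to 5 years (assumed), that is ±1.1 to ±1.4 years.

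**What an imbalance does to the estimate.** The protocol gives no age effect, so the odds ratios per SD of age are assumptions. Take a logistic risk with overall mean 7%, no treatment effect, and mean age shifted by d/2 down in one arm and up in the other. The expected risk ratio, younger arm over older arm, is:

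| Assumed OR per SD of age | d = 0.2 SD | d = 0.3 SD |
|---|---|---|
| 0.74 | 1.06 | 1.09 |
| 0.61 | 1.09 | 1.15 |
| 0.50 | 1.13 | 1.21 |

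The right-hand column needs an imbalance that has only a 3.4% chance at 100 per arm.

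**Type I error and power.** About 2,000 trials per scenario were simulated at 100 per arm, with logistic regression fitted with and without age. Assumed: age SD 4.5 years and odds ratio 0.95, 0.90 or 0.85 per year.

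- No treatment effect (7% in both arms): rejection rate 3.5 to 3.8% without age and 3.6 to 4.1% with age. Neither exceeds 5%.
- 7% against 24%: power 92.0, 93.1 and 93.4% without age; 92.5, 93.3 and 94.8% with age. The gain is about 0.2 to 1.5 points. Each power estimate carries a simulation error of about √(0.93 × 0.07 / 2000) = 0.6 points, so the smaller gains should not be over-read.

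**The case against.** Several stronger readings are tempting, and the protocol does not support them.

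- *That the plan claims equivalence without a margin or a test.* The objective is superiority, and the word is loose language for balance through randomisation. No margin is called for. A baseline significance test would not help either, because after sound randomisation any difference is due to chance.
- *That nothing is adjusted for.* The same section specifies a multivariable model with treatment group and four candidates. Only the absence of age can be criticised. AMH and antral follicle count may carry part of the age signal, although the protocol does not say so and selection could drop both.
- *That the protocol itself calls age prognostic throughout.* The exclusion criterion gives this reason only for women of 42 or over. That age also matters below 42 is a reasonable inference, not a statement in the text.
- *That imbalance could never be seen.* Demographic data are collected and nothing forbids a baseline table, which may well be in a statistical analysis plan. Its absence from the protocol is not a fault.
- *That allocation is simple randomisation.* The text does not say whether the list is blocked. It supports only that no stratification is stated.

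The size is also modest. The planned effect is a risk ratio of 0.24 / 0.07 = 3.4, against which a shift of 1.06 to 1.13 is small, and the age effects behind that shift are assumed.

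What stands is that the baseline sentence is poorly worded, and that a list the protocol chose to state omits a routinely held baseline variable and guarantees none of its members a place in the model.

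**Conclusion.** The point holds as a modest, worthwhile improvement. The protocol names its covariates, leaves out female age, and relies on assumed balance. At 100 per arm there is a 15.7% chance of an age imbalance of 0.2 SD or more in one direction or the other. If the odds ratio per SD of age lies between 0.74 and 0.50, such an imbalance moves a null risk ratio to about 1.06 to 1.13.

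This is not a systematic bias. Over all randomisations the unadjusted test keeps its type I error, and the sample size is unaffected. The imbalance probabilities depend only on the number per arm and unstratified allocation. The shift in the risk ratio and the power gain rest on age effects that the protocol does not supply.

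**What to change.** Replace the equivalence sentence with: *Baseline characteristics will be tabulated by arm without significance tests.*

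Add: *The primary live-birth comparison will be adjusted for female age as a continuous covariate, specified in advance and always retained, and not subject to lasso or stepwise selection. The unadjusted risk ratio will be reported alongside.*

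Because the plan reports a risk ratio but names logistic regression, the same place should say how the adjusted risk ratio is obtained, for example by standardising the predicted risks from the logistic model over all randomised women.

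The cost is a few sentences in the analysis section. Age should already be among the demographic data collected, so no extra participants, visits or measurements are needed.
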